**Inclusion criteria**
Aged 18 years or moreCan read and write in EnglishReceiving medical care for HIV treatment at Vivent Health (confirmed by electronic health record review)At least 1 of the following requirements must be met based on self-report: have a self-reported lapse in medication, which is defined as missing 2 or more doses of medication within a 1-month period; have missed at least 1 appointment while receiving medical care at a Vivent Health clinic; have a history of, or current, substance use disorder, or a report that substance use has caused problems for them at some point in their life

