Power and sample size calculations will be based on the study by Hemming and Taljaard [49]. For a stepped-wedge design with 8 clusters stepped in 1 to 2 clusters at a time over 5 time periods and an assumed intraclass correlation coefficient of ρ=0.10, the design effect relative to an individual-based randomized controlled trial is 3.0. Preliminary data suggest the percentage of enrolled patients with nonsuppressed viral load (HIV RNA ≥200) before intervention to be 26.7%. On the basis of consultation with clinic leadership and pilot data from a single site, we assume a meaningful effect size to be a 10 percentage point reduction in nonsuppressed HIV RNA tests in the study sites after intervention, to 16.7%. The 8 clinical sites average 526 active patients per site per year for an estimated total of 4208 potential patients. We aim to reach approximately 15% of clinic patients using patient engagement strategies geared toward helping those patients most likely to benefit from the clinic-supported intervention. We hypothesize that the implementation strategy can effectively reach 631 (15%) patients and achieve a 68% improvement in viral load suppression among this highly vulnerable population. On the basis of these assumptions, with 3682 active patients, our power to detect a 10 percentage point reduction in nonsuppressed viral loads will be 98.5% (1–β=.985). The study will be sufficiently powered (>80%) to detect up to a 7 percentage point reduction in patients with nonsuppressed viral load.

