The preliminary estimate for the number of patients who are expected to be eligible for the clinic-supported research protocol is shown in Figure 1. Using the criteria described in the Methods section, we identified 1727 patients with evidence of SUD diagnosis or a previous prescription for a SUD medication during the pretrial period. On the basis of laboratory and visit data in the EHR, 1355 (22.45%) patients had 1 or more nonsuppressed HIV RNA tests, and 2798 (46.36%) patients missed 2 or more HIV care visits. We estimate that the 3816 (63.23%) total patients meeting at least 1 of these 3 criteria will be eligible for the clinic-supported version of the intervention. Table 3 provides the study enrollment and intervention implementation timeline. Primary analyses are expected to be completed by 2028.

**Table 1 table1:** Sociodemographic characteristics of patients receiving HIV care at 8 participating medical home clinics between December 2021 and November 2023 (N=6035).

Characteristics			Medical home clinics														
			Milwaukee (n=1480)		Denver (n=1453)		Green Bay (n=240)		St Louis (n=1409)		Austin (n=754)		Kenosha (n=219)		Madison (n=170)		Kansas City (n=307)
Age (y), mean (SD)			47 (13.4)		48.7 (13.1)		48.1 (12.9)		45.2 (12.3)		42.8 (12.7)		45.7 (14.3)		45.4 (13)		41.7 (12.1)

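### The stated 15% reach and 68% improvement do not produce the 10-point site-wide fall in nonsuppression on which the 98.5% power rests

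*Protocol article*

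**What the plan says.** All the figures for the power claim stand in the last paragraph of the protocol article's section Analytic Strategy: Effectiveness and Maintenance.

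- Baseline: "Preliminary data suggest the percentage of enrolled patients with nonsuppressed viral load (HIV RNA ≥200) before intervention to be 26.7" percent.
- Effect: "a 10 percentage point reduction in nonsuppressed HIV RNA tests in the study sites after intervention, to 16.7" percent. The article calls this a meaningful effect, chosen after consultation with clinic leadership and from pilot data at one site.
- Population: "The 8 clinical sites average 526 active patients per site per year for an estimated total of 4208 potential patients".
- Reach: "We aim to reach approximately 15% of clinic patients using patient engagement strategies".
- Effect in those reached: "the implementation strategy can effectively reach 631 (15%) patients and achieve a 68% improvement in viral load suppression". The scale of the 68% is not given.
- Power, stated as following from these assumptions and for 3682 active patients: "our power to detect a 10 percentage point reduction in nonsuppressed viral loads will be 98.5" percent. The article adds that a 7-point reduction is detectable with more than 80% power.

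Three other places bear on this. Study Outcomes says both outcomes are examined at clinic level. The inclusion criteria admit a patient on any one of three self-reported grounds: a medication lapse, a substance use history, or to "have missed at least 1 appointment while receiving medical care at a Vivent Health clinic". None of them is a viral-load criterion. Results reports that "1355 (22.45%) patients had 1 or more nonsuppressed HIV RNA tests" and estimates 3816 patients as eligible for the clinic-supported intervention.

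**The concern.** The model switches the intervention indicator from 0 to 1 for a whole site, so the effect it estimates is an average over all active patients of that site. The article assumes benefit only in the 15% who are reached. Among those, a patient who is already suppressed, and would remain so, cannot add to the fall in nonsuppression. The clinic-wide effect therefore depends on how many of the reached patients are nonsuppressed, and the power paragraph leaves that factor out.

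Viral nonsuppression is one of two primary effectiveness outcomes. If the true clinic-wide effect is a few points, the trial has far less power than the article tells its readers, and a null result could be misread as evidence that ART-C does not work.

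**Working it through.** **1. Reproduce the stated power.** Inputs from the power paragraph: N = 3682 (7 × 526; the eight-site total is 8 × 526 = 4208), design effect 3.0, p1 = 0.267, p2 = 0.167. Alpha is not stated there; 0.05 two-sided is assumed.

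- Effective n per arm = 3682 / 3.0 / 2 = 613.7.
- Power = Φ[(d√n − 1.96·√(2p̄(1−p̄))) / √(p1(1−p1) + p2(1−p2))], where d = p1 − p2 and p̄ is the mean of p1 and p2.
- For d = 0.10: (0.10 × 24.77 − 1.96 × 0.583) / 0.579 = 2.31, so power is 98.9%, against 98.5% stated.
- For d = 0.07: 82.8%, in line with the stated figure above 80%.

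The power formula holds, so the question is where the 10 points come from.

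**2. What the reach assumptions need in order to give 10 points.**

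631 × 0.68 = 429, and 429 / 4208 = 10.2 points. This matches the powered effect, but it counts 68% of everyone reached as a conversion from nonsuppressed to suppressed. The possible meanings of 68% are:

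| Meaning of 68% | What 10 points would require |
|---|---|
| Relative reduction in nonsuppression | 0.10 / (0.15 × 0.68) = 98% of those reached nonsuppressed |
| Percentage points | at least 68% of those reached nonsuppressed |
| Relative gain in suppression | not attainable: the largest gain is 1 − 1/1.68 = 0.405, and 0.15 × 0.405 = 6.1 points |

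**3. What the article says about those reached.** It gives 26.7% nonsuppressed for enrolled patients. Its Results give 1355 / 3816 = 35.5% of the estimated eligible pool with at least one nonsuppressed test in two years.

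**4. The clinic-wide effect implied.** Fall = reach × nonsuppression among those reached × 0.68, with no effect in the other 85%. Power uses the step 1 formula with clinic baseline 26.7% and N = 3682.

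| Nonsuppressed among those reached | Fall, points | Power |
|---|---|---|
| 26.7% (article, enrolled patients) | 0.15 × 0.267 × 0.68 = 2.7 | 19% |
| 35.5% (article, pool average) | 0.15 × 0.355 × 0.68 = 3.6 | 31% |
| 50% (illustration of targeting) | 0.15 × 0.50 × 0.68 = 5.1 | 55% |
| 100% | 0.15 × 1.00 × 0.68 = 10.2 | 99% |

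With N = 4208 the first three powers become 22%, 35% and 61%. In patient numbers, the first row is 0.267 × 631 = 168 nonsuppressed, 0.68 × 168 = 115 converted, and 115 / 4208 = 2.7 points.

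**5. Reading the effect as one among enrolled patients only.** A 68% relative reduction from 26.7% is 0.68 × 26.7 = 18 points, not 10; a fall from 26.7% to 16.7% is a 37% relative reduction. The sample would be 631 rather than 3682, and the same formula gives 42% power for 10 points.

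**The case against.** The strongest reply is that the article states power to detect 10 points, and that power is computed correctly. A trial may be powered for an effect judged meaningful, and this one was chosen with clinic leadership and single-site pilot data. This stands in part: a reader might infer that 98.5% is a miscalculation, and it is not. The article does, however, also present the power as resting on the reach and 68% assumptions, and those do not lead to 10 points.

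Second, ART-C is more than the 631 enrolled patients. At rollout every client may use the app, with peer mentors and an HIV forum. A reader might therefore infer from the figures above that the design cannot deliver 10 points. The documents do not show that. They show only that the stated reach and effect assumptions do not deliver it, and that no effect is stated for anyone else. To close the gap the other 85% would need a fall of (10 − 3.6) / 0.85 = 7.5 to (10 − 2.7) / 0.85 = 8.6 points.

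Third, 35.5% is an average over the eligible pool, not a ceiling for those enrolled. The 1355 nonsuppressed patients outnumber 631, recruitment is meant to favour those most likely to benefit, and Intervention Overview lists viral load among the risk factors. The pool was also counted on EHR criteria that differ from the self-report entry criteria. So it would be too strong to say that underpowering is nearly certain. Targeting could raise the share, which is why 50% is shown. But nothing in the inclusion criteria selects on viral load, and recruitment works from a list of all HIV patients, so a share near 98% has no support in the article.

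Fourth, it would be too strong to say that every enrolled patient must be nonsuppressed. The figure is 98% on one reading of 68% and at least 68% on another.

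**Conclusion.** The power paragraph is wrong as written. No reading of 15% reach, 68% improvement and 26.7% nonsuppression among enrolled patients gives a 10-point fall at site level through the patients reached. On the article's own rates the implied fall is 2.7 to 3.6 points, with power of about 19% to 31%. With half of those reached nonsuppressed it is 5.1 points and about 55%. All three lie below the 7 points that the article says it can detect with more than 80% power.

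This rests on four assumptions: 68% is a relative reduction in nonsuppression, patients not enrolled have no effect (the article states none), the design effect of 3.0 applies to N = 3682, and alpha is 0.05 two-sided. A real effect of the app in the wider clinic population, or strong enrichment of enrollees for nonsuppression, would raise the figures; the article quantifies neither.

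**What to change.** In the power paragraph:

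1. State the scale of the 68%: relative reduction in nonsuppression, percentage points, or relative gain in suppression.
2. State whose rate 26.7% is (enrolled patients or all active patients), and whether it counts patients or tests.
3. Derive the clinic-wide effect openly as reach × nonsuppression among those reached × relative reduction, plus any effect assumed in patients not enrolled, with its basis.
4. Restate power over the resulting range. Keep 98.5% only as the power for a 10-point effect, and say that the reach assumptions do not support that effect.

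Optionally, pre-specify a secondary stepped-wedge contrast in patients whom the EHR flags as nonsuppressed at the start of each period, in control and intervention periods alike. It does not depend on enrollment, and dilution by already suppressed patients is removed.

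The cost is a change of wording and, for the optional analysis, a flag built from EHR data already collected. The stated power becomes less favourable, and the subset is smaller than the clinic population.

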### Study Setting and Patient Population

ART-C will be implemented within 8 HIV medical home clinics operated by Vivent Health in Colorado, Missouri, Texas, and Wisconsin. The HIV medical home model provides HIV-oriented comprehensive care to people living with HIV and encompasses primary health care, dental care, mental and behavioral health services, case management, housing, prevention or harm reduction services, and food bank services.

To describe the baseline, preintervention occurrence of study outcomes, we defined a cross-sectional sample of active patients who would be eligible to receive ART-C as of December 2023. The baseline sample excluded patients who never attended a medical visit, died before the time of study approval, or did not speak English.

Demographic and clinical characteristics of the study sample were captured from the Vivent Health EHR (Epic Systems Corporation). The prevalence of SUD was determined based on visit diagnoses and problem list entries in the EHR, using the *International Classification of Diseases, 10th Revision,* codes (F10-16, F19, O35.4, O35.5, O99.31, and O99.32). Patients were also classified as having SUD if they were ever prescribed a medication to treat alcohol use disorder (acamprosate, disulfiram, topiramate, or naltrexone) or opioid use disorder (methadone, buprenorphine, or naltrexone). For medications that are used for the treatment of SUD and other conditions, patients were only considered to have SUD if the prescription order was paired with an appropriate diagnosis code for alcohol use disorder or opioid use disorder.

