### Analytic Strategy: Effectiveness and Maintenance

In the stepped-wedge design, each site functions as its own control or usual care group before the implementation of ART-C. During this period, clinics treat patients with HIV using existing, standard treatment protocols and do not yet have access to the Connections app. To characterize intervention effectiveness, we will model site, time, and intervention status as predictors of primary outcomes using a repeated measures model to control for clustering by individuals and sites [47]. An indicator variable for intervention status will be modeled as 0 before intervention and 1 after ART-C is rolled out at each site. Random effects will be used to model the correlation between individuals within the same cluster (ie, site) in the stepped-wedge design. For a design with 8 clusters, 5 time points, and N individuals sampled per cluster per time interval, Y_ijk_ will be the response corresponding to individual k at time j from cluster i (i in 1,..., 7; j in 1,..., 8; k in 1,..., N) and Y_ij_ will be mean for cluster i at time j:

Y_ij_ = µ+ α_i_ + β_j_ + X_ij_θ

In this equation, α_i_ is a random effect for cluster i, β_j_ is a fixed effect corresponding to time interval j, X_ij_ is an indicator of the treatment status in cluster i at time j (1=intervention; 0=control), and θ is the treatment effect. The individual-level responses of no-show rates and viral suppression are binary, so the cluster-level responses Y_ij_ are proportions with variance σ_ij_^2^_e_ = µ_ij_ * (1 – µ_ij_). A variance inflation factor of 1 + (N – 1) ρ is incorporated into the analysis, where ρ is the intraclass correlation coefficient between individuals within the same cluster. Logistic generalized estimating equation (GEE) models will be determined using R statistical software (version 4.3.3; R Foundation for Statistical Computing) with geeglm (family=binomial) [48].

After establishing the base model, we will include potentially confounding and moderating factors by adding covariates, interaction terms, and weighting methods to the models. Potential clinic-level confounders will include the racial and ethnic categories, gender, age, and diagnosis of a SUD.

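### The model indices and the sample size behind the stated power do not match the 8-clinic, 5-period design (3682 = 7 × 526); the slip is conservative but needs correcting

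*Protocol article*

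**What the plan says.** The section Study Setting and Patient Population fixes the number of clinics: "ART-C will be implemented within 8 HIV medical home clinics operated by Vivent Health". Table 3 starts them in four pairs, two quarters apart.

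The section Analytic Strategy: Effectiveness and Maintenance introduces the primary model with "For a design with 8 clusters, 5 time points, and N individuals sampled per cluster per time interval". In the same sentence it gives the index ranges as "i in 1,..., 7; j in 1,..., 8; k in 1,..., N", which means 7 clusters and 8 times.

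The power paragraph of that section assumes "8 clusters stepped in 1 to 2 clusters at a time over 5 time periods", "an assumed intraclass correlation coefficient of ρ=0.10", and that "the design effect relative to an individual-based randomized controlled trial is 3.0". It gives the patient base as "The 8 clinical sites average 526 active patients per site per year for an estimated total of 4208 potential patients" and takes 631 patients as 15% of that base. The power statement then begins "On the basis of these assumptions, with 3682 active patients". It reports 98.5% power for a fall in nonsuppression from 26.7% to 16.7%, and more than 80% for a 7-point fall.

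**The concern.** Four details of one section disagree with the design stated around them:

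- **Clusters:** 8 in the text, 7 in the index.
- **Periods:** 5 in the text, 8 in the index.
- **Patients:** 4208 and 3682 in the same paragraph.
- **Steps:** one or two clinics at a time in the text, always two in Table 3.

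The third matters most, because 3682 is the sample size attached to the only power figure in the article. A reader cannot tell whether the calculation was done for this trial or for one with a clinic fewer. The period count matters because the model has one fixed effect per period and the design effect depends on the number of steps, so the model and the power calculation should use the same count.

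**Working it through.** **Patient numbers**

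- 8 × 526 = 4208 and 7 × 526 = 3682, both exact.
- 0.15 × 4208 = 631.2, which is the article's 631. 0.15 × 3682 = 552.3. The reach target therefore uses the 8-clinic base and the power statement uses the 7-clinic number.

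**Steps and periods**

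- Eight clinics in four pairs always step two at a time. Seven clinics in four steps would need one single-clinic step, which is what one to two at a time describes.
- One half-year before the first crossover plus four half-yearly steps gives 5 periods. Table 3 covers 16 quarters, or 8 half-years. Either number can be read from Table 3, but they are not the same design.

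**Which layout the design effect of 3.0 fits**

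The standard stepped-wedge design effect for k steps, one baseline period, one measurement per step and m patients per clinic-period is

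DE = [1 + ρ(km + m − 1)] / [1 + ρ(km/2 + m − 1)] × 3(1 − ρ) / [2(k − 1/k)],

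multiplied by k + 1 periods to apply to the total number of patients.

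- k = 4, ρ = 0.10, m = 526/5 = 105.2: (53.5 / 32.46) × 0.36 = 0.593, and × 5 = 2.97. For m from 92 to 526 the result is 2.96 to 2.99, which matches 3.0.
- k = 7 (8 periods): 2.76 to 2.80 for m from 66 to 526, which does not match.

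The design effect is thus that of the 5-period layout, paired with a 7-clinic patient number.

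**Reproducing the stated power**

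Alpha is not stated, so two-sided 0.05 is assumed. With n = N / 3.0 / 2 per arm and p̄ the mean of the two proportions,

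power = Φ{[Δ − 1.96 √(2p̄(1 − p̄)/n)] / √[(p₁(1 − p₁) + p₂(1 − p₂))/n]}.

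- N = 3682, n = 613.7, 26.7% vs 16.7%: (0.100 − 1.96 × 0.02353) / 0.02336 = 2.31, power 98.9%.
- N = 3682, 26.7% vs 19.7%: (0.070 − 1.96 × 0.02410) / 0.02401 = 0.95, power 82.8%.

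Both agree closely with the article's 98.5% and more than 80%.

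**The same calculation for the design described**

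- N = 4208, n = 701.3, 10 points: (0.100 − 1.96 × 0.02201) / 0.02185 = 2.60, power 99.5%.
- N = 4208, 7 points: (0.070 − 1.96 × 0.02254) / 0.02246 = 1.15, power 87.5%.

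**Cross-check with the Hussey–Hughes variance**

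Inputs: ρ = 0.10, 5 periods, patients divided evenly over clinic-periods, total variance the average of the two binomial variances, two-sided 0.05.

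Var(θ) = Iσ²(σ² + Tτ²) / [(IU − W)σ² + (U² + ITU − TW − IV)τ²].

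For 8 clinics in pairs, I = 8, T = 5, U = 20, W = 120, V = 60. At 10 points the total variance is 0.1674, so τ² = 0.01674 and σ² = 0.9 × 0.1674 / 105.2 = 0.001432. The SE is 0.0217.

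| Clinics, patients | Per clinic-period | 10 points | 7 points |
|---|---|---|---|
| 7, 3682 | 105.2 | 98.8% | 81.8% |
| 8, 3682 | 92.0 | 99.1% | 83.5% |
| 8, 4208 | 105.2 | 99.6% | 88.0% |

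**Optional sensitivity range**

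The article's model has a clinic effect and period effects but no clinic-by-period variation. If a cluster autocorrelation below 1 is assumed (no value is given in the article), 7-point power with 8 clinics and ρ = 0.10 is:

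| Cluster autocorrelation | 105 per clinic-period | 526 per clinic-period |
|---|---|---|
| 0.95 | 70% | 94% |
| 0.90 | 57% | 76% |

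The 526 column treats every active patient as measured in every period and the samples as independent, so it is an upper bound.

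**The case against.** The strongest reply is that nothing of substance is lost. The power paragraph names 8 clusters and 5 periods, its design effect fits Table 3, and correcting the patient number raises power. That stands, and it limits the point to a consistency error. It does not remove the error, because the article gives a power figure for a number of patients that its own text does not support.

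Three stronger readings are tempting and are not supported.

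- **That the 98.5% shows a 7-clinic calculation.** It does not. At 3682 patients, 7 and 8 clinics give 98.8% and 99.1%, too close to separate. Only the exact product 7 × 526, the cluster index ending at 7 and the step wording point to seven clinics.
- **That the claim of more than 80% power for 7 points is false.** The lower figures in the sensitivity range come from an autocorrelation that the article does not supply, and they depend heavily on how many patients are counted per clinic-period. They contradict nothing in the text.
- **That the conflict between 5 and 8 periods leaves the primary analysis data undetermined.** The article does not say so. The 8 may simply count Table 3's half-years, and period boundaries may be set in the full protocol or analysis plan, which are not shown.

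**Conclusion.** The section contradicts itself on the number of clusters, the number of periods, the patient total and the clinics per step. The stated power is attached to 3682 patients, one clinic's worth (526) fewer than the 4208 given in the same paragraph, without explanation. An origin in a 7-clinic plan is likely but remains an inference.

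The error is conservative. Moving to 8 clinics and 4208 patients raises power by about 0.6 points for the 10-point effect (98.9% to 99.5%) and by about 4.6 points for the 7-point effect (82.8% to 87.5%; about 88% by the cross-check). A reader might infer from the wrong patient number that the trial is underpowered. The documents do not support that: both adequacy claims hold under the plan's own assumptions of ρ = 0.10, 5 periods and no clinic-by-period variation. The result also rests on two-sided alpha 0.05, which is assumed here.

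**What to change.** In the section on the effectiveness and maintenance analysis:

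1. Index clusters from 1 to 8.
2. State one number of periods, show how it maps to Table 3, and use it in both the model and the power calculation. The design effect of 3.0 already corresponds to 5.
3. Replace one to two clinics at a time with two clinics per step.
4. Restate the sample size and power for 4208 patients (about 99.5% for 10 points and about 88% for 7 points), with the alpha level. Alternatively, state the exclusion that reduces 4208 to 3682.
5. Optionally, add a sensitivity range for clinic-by-period variation, clearly labelled as an assumption.

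The first four items cost a short recalculation and a few words, and leave the stated claims intact. The fifth might show a less comfortable margin for the 7-point effect, which is worth knowing but is not needed to correct the inconsistency.
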